**Trial registration number:**

NCT02995005, Pre-results.

Strengths and limitations of this studyThis prospective cohort study will inform the optimal time to initiate tenofovir disoproxil fumarate (TDF) treatment in pregnant women to reduce hepatitis B virus (HBV) DNA to undetectable concentrations (defined as <100 IU/mL) prior to birth, which is a strength since this is currently unknown.Strategies for prevention of mother-to-child transmission (MTCT) of HIV are not immediately transferable to HBV so another strength is that this study investigates the feasibility of implementing the recommended treatment for HBV in pregnant women in a limited-resource setting.It is important to identify challenges to adherence and safety in a context of low literacy where two-thirds of pregnant women have limited education to ensure that potential implementation of this strategy is feasibleThis study investigates TDF usage during pregnancy for prevention of MTCT as a potential alternative to hepatitis B immunoglobulin (HBIG), which remains too expensive and difficult to obtain in most limited-resource settings, and will inform future studies that forgo HBIG.This study investigates TDF in addition to HBIG and vaccination in infants born to hepatitis B e antigen-positive mothers as this is the most comprehensive way to prevent MTCT, but such a design does not provide information on the proportion of MTCT in women with an undetectable HBV DNA without HBIG.

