### Study recruitment and enrolment

Pregnant women aged 16–49 years with a singleton viable pregnancy, an HBV infection, and an estimated gestational age of 12 to <20 weeks determined by ultrasound will be counselled about the disease and invited to participate in the study. Part of this information session will include counselling on HBV in general, the need for adherence to the study drug and benefits and risks of the treatment. If a woman is interested, a blood sample will be collected to determine if she meets the criteria for enrolment, that is, HBeAg positive or HBV DNA >1.9 log 10 (>85 IU/mL). Women will be informed of the results at the next visit and be enrolled and started on TDF if all inclusion criteria are met (table 1).

**Table 1 T1:** Inclusion and exclusion criteria

Inclusion criteria	Exclusion criteria
Willing and able to give informed consent for participation in the study	Negative qualitative HBV DNA if HBeAg negative
Hepatitis B infected (HBsAg confirmed positive and qualitative HBV DNA positive in HBeAg-negative mothers)	HIV positive or on immunosuppressive therapy for other illnesses
Female, 16–49 years	Elevated creatinine (>1 mg/dL)
EGA 12–20 weeks at start TDF	Abnormal serum phosphate (<2.4 and >4.5 mg/dL)
Willing to take TDF daily during pregnancy	History of kidney disease
Plans to deliver at SMRU	History of pregnancy complications

EGA, estimated gestational age; HBeAg, hepatitis B e antigen; HBsAg, hepatitis B surface antigen; SMRU, Shoklo Malaria Research Unit; TDF, tenofovir disoproxil fumarate.

SMRU has conducted research for over two decades and the trust in antenatal services is high resulting in high follow-up rates in ANC as well as in previous studies.^36^ If a woman misses an appointment, she will be contacted using her phone number if applicable or the healthcare workers will reach out to her community or family to find her.

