#### Laboratory tests

A maternal whole blood sample obtained by venipuncture will be collected at study entry, monthly until delivery, at birth and at two postpartum visits (figure 2). Maternal HBV DNA, alanine aminotransferase (ALT) and creatinine will be measured at all scheduled visits for the mother. Serum phosphate will be measured at baseline and at birth.

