### Data analyses

#### HBV viral kinetics

The Kaplan-Meier method will be used to estimate the median time from initiation of TDF to an HBV DNA <100 IU/mL including all women and then, based on the distribution of HBV DNA, stratified by high versus low HBV DNA groups. We expect those with low HBV DNA at enrolment to have <100 IU/mL at the time of delivery, but it is important to include them in this study to calculate the trajectory of decline and determine how long they need to be treated to reach HBV DNA <100 IU/mL. A generalised estimating equation model will be used to assess whether baseline HBV DNA and adherence to TDF are associated with the logarithmically transformed HBV DNA over time. A proportional hazard model will be constructed to assess the HR of reaching undetectable HBV DNA adjusting for the baseline HBV DNA concentration and adherence to TDF (# pills actually taken/# pills that should have been taken). For missing HBV DNA data, depending on the reasons for being missing, imputations using multiple imputations by chained equations will be used. Sensitivity analyses will then be performed comparing analyses using complete and imputed data sets. The proportion of women with undetectable HBV DNA at delivery will be reported with 95% CI in all women and by high versus low HBV DNA groups. Median and IQR of HBV DNA at baseline and each visit will be reported. Then, HBV DNA will be logarithmically transformed and the median HBV DNA at baseline and at delivery will be compared using paired t-tests. Additional analyses may be conducted to further explore the data.

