#### Adherence

The main analysis to determine adherence will be calculating per cent adherence using pill counting data (# pills actually taken/# pills that should have been taken). As a confirmation of adherence, we will also measure TDF concentration in all women with detectable HBV DNA at delivery and in a matched subset of women who become undetectable for comparison (n=2× the number of women who do not become undetectable). This is anticipated to include 10–15 women who are HBV DNA detectable at delivery and matched to 20–30 women who are undetectable. This analytical subsample will be matched on age and initial DNA concentration or, if a matched pair analysis is not feasible because no ‘matching partners’ exist, we will correct for these factors using multivariate regression methods.

The ‘Adherence Starts with Knowledge’ questionnaire ASK-12 is a tool to determine adherence and is derived from the ASK-20 questionnaire.^41^ The questionnaire consists of 12 items related to drug adherence in three scales ‘forgetfulness’, ‘treatment beliefs’ and ‘behavior’. Although previous studies have demonstrated the usefulness of ASK-12 for patients, this tool has not been validated in this study population.^42 43^ Local pilot testing has resulted in a culturally appropriate version of this questionnaire and personnel will be trained to use it. We will use pill counts (gold standard) as well as TDF blood concentration (confirmatory) to validate this tool. The results will be analysed by first comparing differences among the groups, one-way analysis of variance and Bonferroni's multiple comparison tests.

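### The baseline-to-delivery comparison names medians but uses a test of means, and the GEE on log HBV DNA is attenuated if the many values below 100 IU/mL are not quantified

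*Protocol article*

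**What the plan says.** The HBV viral kinetics section plans two analyses of HBV DNA as a continuous quantity.

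- **Paired comparison.** After log transformation, "the median HBV DNA at baseline and at delivery will be compared using paired t-tests".
- **Longitudinal model.** A GEE assesses whether baseline HBV DNA and adherence "are associated with the logarithmically transformed HBV DNA over time". Under Laboratory tests, samples are "collected at study entry, monthly until delivery, at birth and at two postpartum visits".

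Three other statements bear on these. The strengths and limitations list speaks of "undetectable concentrations (defined as <100 IU/mL". Study recruitment and enrolment admits women who are "HBeAg positive or HBV DNA >1.9 log 10 (>85 IU/mL". The Adherence section, describing the tenofovir concentration subsample, says: "This is anticipated to include 10–15 women who are HBV DNA detectable at delivery".

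The viral kinetics section also plans Kaplan-Meier estimation, a proportional hazards model, the proportion undetectable at delivery with a 95% CI, and the median and IQR at each visit. Chained-equation imputation is named for missing HBV DNA.

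**The concern.** There are two separate issues.

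The first is an error in the sentence itself. A paired t-test on log values asks whether the mean within-woman log difference is zero, which is a ratio of geometric means on the original scale. It does not compare medians.

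The second is conditional. The protocol anticipates that nearly all women will be below 100 IU/mL at delivery. If the laboratory reports many of those results only as below a limit, their logarithms exist only after a number has been put in. The estimated mean fall then partly reflects that number. In the GEE, a woman who starts low reaches the floor early and then contributes monthly values that cannot fall further. Treating them as exact flattens the time trend and shrinks the coefficients for baseline HBV DNA and adherence. This matters because the plan includes women with low HBV DNA in order to learn their trajectory of decline, and because poor adherence is named in the Introduction as a barrier to implementation.

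**Working it through.** **Inputs from the protocol.** Evaluable n = 150 and enrolment 170 (Sample size); 10–15 women detectable at delivery (Adherence); undetectable means below 100 IU/mL, or 2.00 log10; the enrolment cut-off of 85 IU/mL is 1.93 log10.

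**The plan's own figure.** n = 1.96² × 0.5 × 0.5 / 0.08² = 150.06, so the stated 150 reproduces. The step to 170 allows for 20/170 = 11.8% attrition.

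**Share below 100 IU/mL at delivery.** q = 1 − detectable/n:

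- n = 150: 135/150 = 90.0% (15 detectable); 140/150 = 93.3% (10 detectable)
- n = 170: 155/170 = 91.2% (15 detectable); 160/170 = 94.1% (10 detectable)

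With q above one half, the delivery median lies below 100 IU/mL whatever the detectable values are.

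**Dependence of the mean on the substituted value.** Mean delivery log10 = q·c + (1 − q)·m, where c is the substituted log10 value and m the mean of the detectable values. Only q·c depends on the rule:

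| Substituted (IU/mL) | c | q·c at q = 0.90 | q·c at q = 0.941 |
|---|---|---|---|
| 100 | 2.00 | 1.80 | 1.88 |
| 85 | 1.93 | 1.74 | 1.82 |
| 50 | 1.70 | 1.53 | 1.60 |
| 10 | 1.00 | 0.90 | 0.94 |
| 1 | 0.00 | 0.00 | 0.00 |

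Choosing 85 instead of 100 moves the mean by at most 0.07 log10; choosing 50 moves it by about 0.3. Only substitutes as low as 10 or 1 move it by roughly 1 or 2 log10. At q = 0.5, the value used in the sample size section, each shift is 0.5/0.90, or about 56%, of its size at q = 0.90.

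**Illustrative simulation.** Assumed, and not in the protocol: 170 women; baseline mean 7.5 log10 in a high group (33% of women) and 3.2 in a low group, SD 0.8; a first-month fall of about 1.8 log10, then 0.8 per month; six monthly visits with the sixth as delivery; exchangeable GEE of log10 HBV DNA on month, baseline and adherence. Every value below 100 IU/mL was treated as unquantified, and 91% were below 100 at delivery.

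| Substituted (IU/mL) | Mean change | Median change | GEE baseline coefficient | GEE adherence, per 10 points |
|---|---|---|---|---|
| 100 | -2.53 | -1.78 | 0.38 | -0.09 |
| 85 | -2.59 | -1.85 | 0.39 | -0.09 |
| 50 | -2.79 | -2.08 | 0.43 | -0.09 |
| 10 | -3.40 | -2.78 | 0.54 | -0.11 |
| 1 | -4.27 | -3.76 | 0.71 | -0.14 |
| No floor | not computed | not computed | 0.99 | -0.40 |

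Four things follow.

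1. With 100 substituted, the mean and median change differ by 2.53 − 1.78 = 0.75 log10, so the two quantities are not interchangeable.
2. The paired t-test has p below 1e-30 under every rule. Only the estimate depends on the rule.
3. The adherence coefficient keeps 0.09/0.40 = 22% to 0.14/0.40 = 35% of its no-floor size. The baseline coefficient keeps 0.38/0.99 = 38% to 0.71/0.99 = 72%.
4. At month 1, 49% of values are already below 100, so about half still carry information from above the floor.

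Varying the high-group share (20–50%) and the later decline (0.7–0.95 log10 per month) gives adherence coefficients of -0.02 to -0.16 against -0.37 to -0.43 with no floor, and 38–63% of values below 100 at month 1.

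**The case against.** **The censoring is not established.** 100 IU/mL is a study definition, not a stated assay limit, and the 85 IU/mL cut-off suggests that some readings below 100 are possible. This stands, and it makes everything beyond the wording error conditional.

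**A rule for values below the limit may exist elsewhere.** The article condenses a fuller protocol, and an analysis plan may exist. This also stands: the absence of such a rule here is not a finding.

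**The share is derived and sits beside a disclaimer.** The protocol states 10–15 women, not a percentage, and the Sample size section says that nothing is known in advance about this proportion. That is fair, but 10–15 is still the article's own anticipation.

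**On the log scale, mean and median may roughly coincide.** That holds if the log differences are symmetric. A mixture of high and low baselines meeting a common floor makes symmetry unlikely, as the 0.75 log10 gap illustrates.

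A reader might go further and infer that the floor determines both analyses. The documents do not support that for the GEE, which uses monthly values, many of them above 100 IU/mL early on. Nor do they support the view that an association with baseline would be a mere artefact. The plan names no baseline-by-time interaction, and for the association with level the floor weakens a real effect rather than creating one. A dramatic swing in the mean fall needs substitution near 1 IU/mL, which the protocol never suggests.

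**Conclusion.** The median/t-test sentence is wrong as written, and this does not depend on any assumption. The remainder holds on the condition that an appreciable share of values below 100 IU/mL is not quantified. In that case the delivery median is known only to be below the limit and the size of the mean log change depends on the coding: at most 0.07 log10 between 85 and 100 IU/mL, more for much lower substitutes. The GEE then understates the baseline and adherence effects. The simulated sizes rest on assumed baselines and decline rates and show direction and rough scale only.

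It would be tempting to conclude that the trial's main result is compromised. It is not. The primary objective is time to below 100 IU/mL, and the Kaplan-Meier estimate, the hazard model and the delivery proportion need only that yes/no status. The point concerns secondary analyses and is minor to moderate.

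**What to change.** 1. Replace the paired t-test with a paired sign test, or a signed-rank test with censored values ranked lowest. Otherwise keep the t-test and name the mean log10 change as the quantity tested.
2. Report the median and IQR with results below the assay limit shown as below that limit, not as a substituted number.
3. Analyse log10 HBV DNA over time with a left-censored (Tobit-type) mixed model including time, baseline HBV DNA and adherence, in place of the GEE or beside it.
4. Where a substituted value is used, including in any retained GEE, add a sensitivity analysis over that value.

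Fitting slopes only up to each woman's first value below 100 IU/mL is not a good substitute, because it truncates on the outcome.

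The cost is a change of wording and modest extra programming, with no new data. The censored model relies on a distributional assumption for the unobserved values, which is a reason to keep the GEE beside it.

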#### Adherence

The main analysis to determine adherence will be calculating per cent adherence using pill counting data (# pills actually taken/# pills that should have been taken). As a confirmation of adherence, we will also measure TDF concentration in all women with detectable HBV DNA at delivery and in a matched subset of women who become undetectable for comparison (n=2× the number of women who do not become undetectable). This is anticipated to include 10–15 women who are HBV DNA detectable at delivery and matched to 20–30 women who are undetectable. This analytical subsample will be matched on age and initial DNA concentration or, if a matched pair analysis is not feasible because no ‘matching partners’ exist, we will correct for these factors using multivariate regression methods.

The ‘Adherence Starts with Knowledge’ questionnaire ASK-12 is a tool to determine adherence and is derived from the ASK-20 questionnaire.^41^ The questionnaire consists of 12 items related to drug adherence in three scales ‘forgetfulness’, ‘treatment beliefs’ and ‘behavior’. Although previous studies have demonstrated the usefulness of ASK-12 for patients, this tool has not been validated in this study population.^42 43^ Local pilot testing has resulted in a culturally appropriate version of this questionnaire and personnel will be trained to use it. We will use pill counts (gold standard) as well as TDF blood concentration (confirmatory) to validate this tool. The results will be analysed by first comparing differences among the groups, one-way analysis of variance and Bonferroni's multiple comparison tests.

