**Laboratory tests**							
HBsAg/HBeAg	X						
HBV DNA	X	X	X	X			
Creatinine	X	X	X	X			
Serum phosphate	X		X				
ALT	X	X	X	X		X*	
TDF concentration			X†				
Cord HBsAg/HBV DNA			X†				
Infant HBsAg					X‡		
Pill count		X	X	X			
Adverse event assessments		X	X	X			
Infant anthropometry			X	X	X	X	X
Infant neurodevelopment							X
Adherence survey		X	X	X			
Infant HB vaccination			X§		X	X	X

*Follow-up will continue if suspected or confirmed flare.

†Cord blood sample.

‡Venepuncture sample blood and only for hepatitis B surface antigen (HBsAg).

§If mother hepatitis B e antigen (HBeAg) positive also hepatitis B immunoglobulins (HBIG).

ALT, alanine aminotransferase; HBV, hepatitis B virus; PP, post partum; TDF, tenofovir disoproxil fumarate.

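### The only analysis named for validating ASK-12, a one-way ANOVA with Bonferroni tests on undefined groups, does not measure how well the score tracks or classifies pill-count adherence

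*Protocol article*

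**What the plan says.** The Adherence section of the protocol article states of ASK-12 that "this tool has not been validated in this study population". It then sets the aim: "We will use pill counts (gold standard) as well as TDF blood concentration (confirmatory) to validate this tool". The method follows in one sentence, which gives it as "first comparing differences among the groups, one-way analysis of variance" together with Bonferroni tests. No second step is named.

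The reference standard is a continuous quantity, obtained by "calculating per cent adherence using pill counting data (# pills actually taken/# pills that should have been taken"). The instrument is described only by its structure: "The questionnaire consists of 12 items related to drug adherence in three scales". The section gives no adherence groups and no cut-off, either for the score or for the pill count.

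In Table 2 the row "Adherence survey" is marked at the monthly visits, delivery and 1 month post partum, and the pill-count row is marked at the same visits. The two measures are therefore paired and repeated within each woman.

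Tenofovir concentration, the confirmatory reference, is to be measured in "all women with detectable HBV DNA at delivery and in a matched subset of women who become undetectable". That is 10–15 detectable and 20–30 undetectable women, matched on age and initial DNA concentration, with a regression fallback if matching fails.

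**The concern.** To validate a questionnaire against a declared gold standard is to ask how closely the score follows that standard, and how well it separates adherent from non-adherent women. One-way ANOVA asks whether mean scores differ between groups. The F test can be clearly significant while the score classifies individuals poorly. Because the groups are undefined and the reference is continuous, it is also unclear which comparison would be made.

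There is a second, conditional issue. One-way ANOVA in its standard form assumes independent observations, whereas each woman contributes several surveys. The article plans a generalised estimating equation for repeated HBV DNA (HBV viral kinetics section) but names nothing comparable for ASK-12.

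The stake is modest but real. The article counts poor adherence among the main barriers to implementing TDF and makes addressing such barriers a secondary objective. A questionnaire declared valid because a significance test was passed could be carried into later programmes on weak evidence.

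**Working it through.** **1. The article's own figure.** The ASK-12 validation has no sample size of its own. The study size in the Sample size section reproduces: n = 1.96² × 0.5 × 0.5 / 0.08² = 150.06, stated as 150, with 170 to allow for attrition. I use 150 women below.

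**2. What a significant ANOVA would show.** Assumptions, none given in the article: one score per woman, score and pill-count percentage jointly normal with correlation r, and three equal groups by pill-count tertile.

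- The tertile means of a standard normal variable are −1.09, 0 and 1.09. The between-group variance of the score is r² × (2/3) × 1.09² ≈ 0.79 r².
- For r = 0.3 this is 0.071, so f² = 0.071 / (1 − 0.071) ≈ 0.077, and the noncentrality is 150 × 0.077 ≈ 11.5.
- The F test on 2 and 147 degrees of freedom at 5% then has power of about 0.86. Simulation agrees.

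| Correlation r | R² | ROC area for the lowest pill-count tertile | Chance that ANOVA is significant |
|---|---|---|---|
| 0.2 | 0.04 | 0.59 | 47% |
| 0.3 | 0.09 | 0.64 | 86% |
| 0.4 | 0.16 | 0.69 | 99% |
| 0.5 | 0.25 | 0.73 | about 100% |

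A score that explains 9% of the variance in adherence would usually pass. The test hardly distinguishes r = 0.4 from r = 0.5 or above.

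**3. Repeated surveys.** The number per woman is not stated. Entry at 12 to <20 weeks and delivery at 37–40 weeks (assumed) give about 4 to 7 four-week intervals. I take 6–8 surveys in total, including delivery and 1 month post partum. The type I error of a nominal 5% three-group ANOVA, by simulation with 150 women, depends on the unit of analysis and on how stable both measures are within a woman:

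- One mean score per woman: about 5% at every within-woman correlation tried (0 to 0.7).
- All surveys pooled, 6 per woman, score correlation 0.3: about 5%, 8%, 13% and 30% when the within-woman correlation of the pill count is 0, 0.3, 0.6 and 1.
- All surveys pooled, 8 per woman, score correlation 0.6: about 5%, 15%, 26% and 58% for the same pill-count correlations.

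The error thus runs from nominal to more than ten times nominal, and the article supplies neither correlation.

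**4. Tenofovir subset.** Total: 10 + 20 = 30 to 15 + 30 = 45 women. Detectable women are one third of the subset, against 10/150 = 7% to 15/150 = 10% of the cohort. The undetectable women are further selected by matching. Results in this subset do not describe the cohort, and reweighting by the detectable and undetectable sampling fractions alone would not undo the matching on age and initial DNA.

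**The case against.** The best defence has five parts.

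- **Known-groups evidence counts.** Different mean scores across pill-count groups are a recognised form of validity evidence, and the word *first* suggests that other steps follow. This stands in part. A reader might infer that the plan cannot show validity at all, and the article does not support that. It supports only that the one named step does not measure association or accuracy.
- **A condensed article may leave details to the full protocol or SAP.** This is true of cut-offs and later steps, whose absence alone would be no finding. But here the article does name a method for a stated aim, and that method fits the aim poorly.
- **Pooling is not stated.** This stands. A reader might infer from Table 2 that the ANOVA has an inflated error rate. The article neither says nor excludes that repeated surveys enter as separate rows, and with one score per woman the test keeps its 5% level. No single inflation figure is justified.
- **A good correlation would not be missed.** This also stands. At 150 women, power is 99% at r = 0.4. The risk is one-sided: a weak tool passes.
- **Little depends on it.** Validating ASK-12 is not a listed objective, adherence is determined mainly by pill count, and the adherence covariate in the proportional hazards model is the pill ratio.

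**Conclusion.** The point holds in a limited form. The article aims to validate ASK-12 against a continuous gold standard, yet the only analysis named compares means of undefined groups. On the assumptions of 150 women, pill-count tertiles and normal data, that analysis would be significant in about 86% of cases at a correlation of only 0.3. It therefore cannot serve as the criterion of validity, although it may contribute as known-groups evidence.

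The repeated-measures issue is conditional on pooling, and its size is unknown because the within-woman correlations of score and pill count are not given. *Agreement* would be the wrong target, since the score and the percentage are on different scales; association and accuracy are what is needed. The tenofovir comparison is sound as confirmation within a matched, outcome-selected subset, but not as a description of the cohort.

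This is a minor point. The primary estimate of time to HBV DNA suppression is not affected.

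**What to change.** Replace the ANOVA sentence in the Adherence section with text on these lines:

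- The main validation analysis is the rank correlation between the ASK-12 score and the pill-count ratio for the same interval, with a 95% CI.
- Discrimination is reported as ROC area, with sensitivity and specificity, for non-adherence at a pill-count cut fixed before the data are examined.
- Confidence intervals are clustered by woman (cluster bootstrap or GEE). Alternatively, one summary score and one summary pill-count ratio per woman are used. State which.
- Any ANOVA with Bonferroni comparisons is kept only as a descriptive known-groups check, with the groups defined.
- The tenofovir comparison is confirmatory within the matched subset, adjusted for age and initial DNA concentration, and is not generalised to the cohort. Simple weighting by sampling fraction is not used.

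The cost is a change of analysis wording and the choice of one cut in advance. Surveys and pill counts are already scheduled at the same visits, so no new data are needed.
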